## Abstract

**Background:**

Digital stories—first-person, self-made, 2- to 3-minute videos—generate awareness, impart knowledge, and promote understanding on topics such as mental illness. Digital stories are a narrative-based art form often created by individuals without formal training in filmmaking to relate personal experiences. Somewhat like digital narratives, video testimonies created within the social marketing or fundraising campaigns of government agencies and private or public corporations aim to reduce the stigma of mental illness while supporting research and services. In video testimonies, personal stories are captured on camera by professional filmmakers. Sharing critical life events greatly benefits tellers and listeners alike, supporting catharsis, healing, connectiveness, and citizenship.

**Objective:**

This study explores digital stories and video testimonies featuring mental illness and recovery in their ability to elicit empathy and compassion while reducing stigma among viewers.

**Methods:**

Using mixed methods, phase 1 will involve a search of Canadian social marketing activities and fundraising campaigns concerning mental illness and recovery. Phase 2 will involve the organization of digital storytelling workshops in which participants will create digital stories about their own experiences of mental illness and recovery. In phase 3, a pilot randomized controlled trial will be undertaken to compare marketing and fundraising campaigns with digital stories for their impact on viewers, whereas phase 4 will focus on knowledge dissemination.

**Results:**

Ethics approval for this study was received in March 2021. Data on the feasibility of the study design and the results of the controlled trial will be generated. This study will produce new knowledge on effective ways of promoting mental health awareness and decreasing stigma, with practical importance for future social marketing and fundraising campaigns. The anticipated time for completion within the 2-year study period includes 9 months for phase 1 (knowledge synthesis activities identifying social marketing and fundraising campaigns) and phase 2 (storytelling workshops), 11 months for phase 3 (feasibility assessment and data collection: randomized controlled trial), and 2 months for phase 4 (knowledge dissemination).

**Conclusions:**

The knowledge generated will have practical implications for the public and for future social marketing and fundraising campaigns promoted by government agencies as well as nonprofit and for-profit organizations by enhancing our understanding of how individuals and societies respond to stories of mental distress and what prompts citizens to help others.

**Trial Registration:**

ClinicalTrials.gov NCT04881084; https://clinicaltrials.gov/ct2/show/NCT04881084

**International Registered Report Identifier (IRRID):**

PRR1-10.2196/33525

## Introduction

### Background

Stories of human distress and struggle are shared daily through news stories and in social marketing and fundraising campaigns using digital formats, including videos [1,2]. Digital narratives are also created for public consumption by ordinary citizens with no formal training in filmmaking to promote awareness of different problems or realities [1]. Digital narratives and video testimonies aim to shape attitudes and stimulate empathy, compassion, and good citizenship among listeners [1,2]. Sharing moments and insights offered by personal experience is invaluable for tellers and listeners alike, promoting catharsis, healing, reconciliation, and social connection [3].

Researchers have studied the portrayal of mental health issues in various media (eg, television and newspapers) since the 1990s [4-7], identifying their impact as overwhelmingly negative. Media depictions abound with stereotypes of persons affected by mental illnesses as dangerous or violent, further contributing to their social marginalization and stigmatization [4-17]. In response, programs such as the Opening Minds campaign [18] have been created to encourage the dissemination of *good media reports* [19] that foster a more humanizing and hopeful understanding of the lived experience of mental illness and encourage help-seeking for mental health problems [20].

Although negative, media-generated portrayals of mental distress remain a serious cultural and social concern, new internet-based media forms offer a wider variety of perspectives [10,11], whether narratives created by government agencies and public or private corporations (video testimonies), or digital stories, a mix of images and text, and the visual arts of private citizens who use the internet to share personal experiences of mental illness as a way of promoting awareness [21,22]. Government or privately sponsored social marketing and fundraising campaigns use video testimonies to promote more positive perspectives, transforming the internet into an educational forum while eliciting financial contributions through organizational websites and social networking venues [23-28].

Preliminary evaluations report mixed results and raise many questions about the effectiveness of social marketing campaigns [29,30]. For example, the Cambridge intervention, which aimed to reduce discrimination against people with mental distress, succeeded in increasing public awareness of mental health issues through advertising to promote arts-based community interventions. However, the results were not sustained beyond the campaign, as has also occurred with other international initiatives [23]. Results of the Systematic Medical Appraisal, Referral, and Treatment Mental Health Project in India involving ≥2000 participants showed improved attitudes toward mental illness and reduced stigma around help seeking following a multimedia intervention that provided print information and a video on mental health [31]. The 2009 Opening Minds initiative of the Canadian Mental Health Commission also used media campaigns for public education on mental illness and stigma, with mixed results [26]. Moreover, the value of sharing recovery stories was not lost on those with lived experience who received training to perform a teaching role in the campaign [30,32]. Outcomes measured in terms of the attitudinal or behavioral intentions of listeners also showed success. The organizers agreed to create more focused, cost-effective, and sustainable grassroots public awareness campaigns following criticism that the Opening Minds campaign had not reached out to ethnic minorities or Indigenous people [29,30,33].

Another successful initiative, Bell Canada’s annual *Let’s Talk* antistigma fundraising campaign, takes on the stigma of mental illness while raising funds to support research and services. Video testimonies feature stories of celebrities such as Clara Hughes, a Canadian Olympic medalist who previously struggled with mental illness. In 2020, the campaign generated >154,173,435 *interactions* that contributed >CAD $7,900,000 (US $6,165,950) to mental health initiatives. Research showed a temporary increase in visits to mental health services among youth in Ontario, Canada, following the *Let’s Talk* campaign [34]. However, this campaign has been criticized for using testimonies that tended to downplay oppressive conditions such as poverty, racism, and violence connected with mental illness [35,36].

Digital storytelling, that is, first-person, self-made, 2- to 3-minute narratives prepared digitally and shared on the web [20,37,38], are viewed by their creators as an opportunity for communicating emotions and thoughts and destigmatize sensitive and marginalizing personal issues while bringing hope and encouragement to others [38]. Storytelling is an age-old tradition that brings people together through shared knowledge and experience [3,39]. Digital stories or short movies that combine personal narratives and images are modern versions of this tradition [32] and an art form that combines emotional charge, authenticity, and simplicity [39,40]. Leading this grassroots movement [40] is the Center for Digital Storytelling, established in the 1990s to promote the creation of digital stories by citizens, from secondary school students to seniors, including those with no knowledge of media production techniques [38].

Given the lack of research on the impact of social marketing and fundraising campaigns [20,41] and the creation and dissemination of digital stories about mental illness by people with no film background, this study examines these 2 storytelling forms (video testimonies presented in social marketing and fundraising campaigns vs digital stories) in terms of their ability to elicit empathy and compassion. Individuals with lived experience of mental illness will be invited to create and share digital stories exploring difficult, vulnerable, and meaningful moments in their lives with full awareness and acceptance of any painful thoughts and feelings they experience. This process will enable them to see their experiences as part of the human condition rather than as personal, isolated, or shameful events.

### Stories, Meanings, and Discourses

As Baldwin [3] describes, human beings are meaning-making creatures defined by and defining themselves through the stories they tell about themselves. Stories evoke emotions that can motivate changes in behaviors, attitudes, beliefs, and even the overall course of lives [3]. Stories bring together different realities, people, places, and times. Viewing stories from various epistemic and ontological standpoints reveals key elements: (1) stories are fluid, as people have many stories to tell and their experiential understandings change over time; (2) sharing stories fulfills the human need for connection; (3) listening to stories can be troubling, but listeners are not always ready to listen deeply; (4) how a life moment is recounted varies with individual experience; and (5) stories are generated by, and generate, discourse, inviting critical analysis [38,40]. Stories also use discourse voluntarily or involuntarily, and new discourses are generated in communicating experiences to others [42-44].

### Empathy and Compassion

Empathy, a key concept, has both cognitive and emotional domains. Cognitively, empathy requires an understanding of another person’s inner experiences, feelings, and perspectives regarding the outside world, whereas the affective domain involves entering the experiences and feelings of the other. The notion of *feeling with* another has been studied by phenomenologists contemplating how subject and object are enmeshed in prereflective existence [45]. Merleau-Ponty [46] described this as “the intertwining of my life with the lives of others, of my body with the visible things, the intersection of my perceptual field with that of others.” Empathy has been criticized from a theoretical standpoint, notably in *On the Problem of Empathy* by the philosopher Edith Stein [45], where she questions whether it is truly possible to feel what another person is feeling.

Compassion, from the Latin *compati,* means *to suffer with*. Compassion, described as the capacity to feel distress for, and desire to alleviate the distress of, another person cuts across theological, philosophical, and psychological traditions [46]. The Dalai Lama defined compassion as “a sensitivity to the suffering of self and others, with a deep commitment to try to relieve it” [46,47], whereas psychological models and therapeutic practices recognize the concepts of compassion and self-compassion [46-49]. The model of self-compassion by Neff [48,49], inspired by Theravada Buddhism, emphasizes cognitive over motivational elements and comprises (1) awareness and openness to distress; (2) kindness; and (3) capacity to share experiences of distress with others without shame, as an act of common humanity. Another example, compassion-focused therapy by Gilbert [50], develops (1) genuine motivation to care for self and others, (2) sensitivity to distress and needs, (3) the ability to connect with one’s pain to heal, and (4) tolerance toward distress in eliciting empathy and compassion.

### Aims and Research Questions

#### Overview

This study explores digital stories and video testimonies about mental illness, particularly those focused on mental health recovery, and how these stories elicit empathy and compassion. The following three questions will be addressed:

How are mental and emotional distress depicted in video testimonies presented in social marketing and fundraising campaigns versus digital stories made by people without formal training in filmmaking?What impact does digital storytelling have on its creators, as people willing to revisit difficult life moments and transform them into digital videos?How do digital narratives (video testimonies and digital stories) elicit empathy and compassion among viewers?

#### Qualitative Research Methodology

Qualitative research methodology will be used to investigate all study activities related to digital storytelling, based on the following three research questions:

What is the value of digital narratives (video testimonies presented in social marketing and fundraising campaigns) and digital stories created by individuals for retheorizing empathy and compassion?How do digital narratives (video testimonies in social marketing and fundraising campaigns) influence empathy and compassion? What emotions emerge when people engage with these digital narratives as viewers?How do digital stories created by ordinary people impact empathy and compassion? What emotions emerge when people engage with digital stories as viewers?

#### Quantitative Research Methodology

A pilot randomized controlled trial (RCT) will be performed as a feasibility study to assess the impact of video testimonies (social marketing and fundraising campaigns) versus digital stories.

The specific quantitative research question is as follows: are digital stories made by people without formal training in filmmaking more effective in eliciting empathy and compassion among viewers than the digital narratives used in social marketing and fundraising campaigns?

Using the Thabane et al [51] typology for feasibility studies, we also developed questions to test (1) process, (2) resources, (3) management, and (4) the scientific basis of our RCT. Examples of questions related to feasibility of the RCT include the following:

Process: what were recruitment rates and refusal rates for participation; how was randomization conducted?Resources: how much time was required to conduct each stage of the protocol? How much time was required to recruit participants (university students)? How adequate was the web-based platform (REDCap [Research Electronic Data Capture]; Vanderbilt University) for collecting data?Management: what was the research team’s capacity, expertise, and availability for completing the planned research activities? Were any important study variables omitted? Do the data show too much or too little variability?Scientific basis: what were the reliability, validity, and trustworthiness of assessments used with the targeted population (university students) for this specific intervention? What was the estimated intervention effect? What was the estimated variance of the intervention effect?

The primary focus of this pilot study will be to gather data on the feasibility of the RCT; however, the following primary and secondary hypotheses have been generated (Textbox 1).

Primary and secondary hypotheses.
**Primary hypotheses**
Change in empathy among participants using the Toronto Empathy Questionnaire [52]Change in compassion among participants using the Compassionate Love Scale [53]

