**Secondary hypotheses**
Change in positive emotions among participants using the Dispositional Positive Emotions Scale [54]Change in mental health self-stigma among participants using the Self-Stigma of Mental Illness Scale-Short Form [53]Change in public mental health stigma among participants using the Difference and Disdain Scales for Public Stigma [55]

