#### Phase 3: Pilot RCT

##### Participants

A parallel 2-arm RCT design will be used to assess the impact of digital stories made by ordinary people compared with digital narratives used in social marketing and fundraising campaigns. A convenience sample of university students (n=80; age 18-35 years) from McGill University will be invited to participate in the pilot RCT, as a population comfortable with accessing web-based visual content and relatively easy to engage within the project timeline.

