### Strengths and Limitations

This mixed methods study is the first to examine digital stories and video testimonies featuring mental illness and recovery in their ability to elicit empathy and compassion among viewers while reducing stigma.

The study will produce important knowledge on effective ways of promoting mental health awareness and decreasing stigma in the public, with practical application for future social marketing and fundraising campaigns.

Generalizability of the findings is limited to the Canadian and North American context, as the digital stories and video testimonies selected and evaluated in this study represent social marketing and fundraising campaigns in Canada or the testimonies of private citizens.

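### The hypotheses are worded as change among participants, although the question and analysis compare arms; the promised public stigma conclusions exceed what two active arms of students can support

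*Protocol article*

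**What the plan says.** Under Quantitative Research Methodology, the protocol article asks whether digital stories are "more effective in eliciting empathy and compassion among viewers than the digital narratives used in social marketing and fundraising campaigns". Textbox 1 then lists two primary hypotheses, "Change in empathy among participants using the Toronto Empathy Questionnaire" and "Change in compassion among participants using the Compassionate Love Scale". The three secondary ones have the same form, for example "Change in public mental health stigma among participants using the Difference and Disdain Scales for Public Stigma". None names an arm, a contrast or a direction. The same section says that the pilot's primary focus is feasibility.

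Under Randomization Procedure, one arm sees digital stories and the other sees campaign videos as an active control. There is no unexposed or neutral-video arm. Under Methods of Assessment and Measurement, the scales are completed at time 1, before exposure. Data Management and Analysis plans a repeated-measures analysis of variance of mean group differences from baseline to postintervention, with a time-by-group interaction.

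The Participants section describes "A convenience sample of university students (n=80; age 18-35 years) from McGill University". Strengths and Limitations states "The study will produce important knowledge on effective ways of promoting mental health awareness and decreasing stigma in the public", and the Results paragraph of the Abstract makes a similar promise. The only limit on generalizability given in Strengths and Limitations is "Generalizability of the findings is limited to the Canadian and North American context".

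**The concern.** Three statements that should agree do not. The research question and the analysis concern a difference between randomized arms. Read literally, the hypotheses concern a change over time in everyone enrolled. The closing claims concern an absolute effect on stigma in the general public.

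The first gap matters because the planned model yields both a time effect and an interaction, and hypotheses worded as change among participants do not say that the interaction decides them. A common rise in empathy would fit the wording of a primary hypothesis without answering the research question.

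The second gap matters because participants are told the study objective at consent (Sampling section) and complete the scales before and after viewing. Retest effects or a wish to give the expected answer could move scores in both arms, and nothing in the design separates such a shift from an effect shared by the two kinds of video.

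**Working it through.** The article gives no significance level, effect size or standard deviation, so there is no derived figure to reproduce. The check has three parts.

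**1. What two active arms can identify.** Let d be a non-specific pre-post shift common to both arms, a the effect of digital stories, and b the effect of campaign videos.
- Expected change with digital stories: d + a.
- Expected change with campaign videos: d + b.
- Time effect (average change with equal arms): d + (a + b)/2.
- Time-by-group contrast: (d + a) − (d + b) = a − b.

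There are two observable quantities and three unknowns. The difference a − b is identified and free of d; neither a nor b is identified alone. A contrast of zero fits a = b = 0 as well as a = b > 0. A claim of relative effectiveness can therefore rest on this design. A claim that either form reduces stigma cannot.

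**2. Illustration.** Inputs: 40 per arm (Randomization Procedure), and the test–retest coefficient of 0.73 given for the Toronto Empathy Questionnaire, taken as the pre-post correlation r (an assumption). Two-sided 5% tests and equal variances at both times are also assumed. In baseline SD units, the SD of change is sqrt(2 × (1 − 0.73)) = sqrt(0.54) = 0.735. In 20,000 simulated trials in which neither video has any effect:

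| Common shift (SD, assumed) | Time effect significant | Interaction significant |
|---|---|---|
| 0.1 | 23% | 5.0% |
| 0.2 | 68% | 5.0% |
| 0.3 | 95% | 4.8% |

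The middle column is not an error rate of the planned group comparison. It shows only why within-arm change should not carry a hypothesis. The last column shows that the randomized contrast is unaffected.

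**3. Baseline adjustment against change scores.** Per-participant variance, in units of the score variance:
- change score: 2(1 − r) = 2 × 0.27 = 0.54;
- post-exposure score adjusted for baseline: 1 − r² = 1 − 0.5329 = 0.467.

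The ratio is 0.467/0.54 = 0.865, a reduction of 13.5%, about 14%. In general the reduction is (1 − r)/2: 25% at r = 0.5 and 5% at r = 0.9. Both analyses estimate a − b under randomization.

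**4. Population.** The sample is 80 students of one university, aged 18-35, recruited by convenience. The public stigma scale records the attitudes of these participants; it does not measure stigma in the population. The stated limit on generalizability is justified by where the videos come from and does not mention who watches them.

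**The case against.** The strongest reply is that the Textbox 1 lines are labels naming a construct and its scale, that they follow directly on a comparative question, and that Data Management and Analysis already targets group differences in change. Much of this stands. A reader might infer from Textbox 1 that this is in effect an uncontrolled pre-post study, or that the time effect is the planned primary test. The analysis section does not support either reading. An active comparator is a legitimate choice for the question asked, and a shift common to both arms cancels in the comparison.

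It is also fair that the article nowhere says a pre-post change will be reported as confirming a hypothesis, that feasibility comes first, and that CONSORT reporting is promised. Baseline adjustment is a gain in efficiency, since the planned interaction is itself valid.

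Finally, the sentence about stigma in the public describes the whole mixed methods project, and the generalizability sentence is about the video material. The article is also open elsewhere about the student convenience sample. But the stigma scales are used only in the trial, and the qualitative work cannot supply the missing unexposed comparison. A limitations section that names only the geographic context leaves out the narrower limit that matters most. Hypotheses and conclusions that the article itself states are not details left to a fuller document.

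**Conclusion.** The point holds as a mismatch between hypotheses, design and claims, not as a fault in the randomized comparison. The hypotheses lack the contrast and direction that the research question and analysis have. A change common to both arms cannot be attributed to the videos, so the claim about effective ways of decreasing stigma in the public does not follow. The generalizability statement omits the single-university student sample.

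A reader might go further and conclude that the trial can say nothing about effectiveness. The documents do not support that: whether one form does better than the other can be estimated from the randomized contrast, with the precision of a pilot.

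The identification argument needs no numerical assumption. The gain of about 14% in variance rests on r = 0.73, which is a test–retest figure for one scale, and on equal variances at both times. The drifts used for illustration are assumed.

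**What to change.** - **Textbox 1:** state each hypothesis as the between-arm difference, digital stories minus campaign videos, in mean post-exposure score adjusted for the time 1 score. For empathy and compassion the research question already implies the direction. For the secondary scales the investigators should state one.
- **Data Management and Analysis:** name this contrast as the one that addresses the hypotheses, report it with a 95% CI, and label within-arm change as descriptive.
- **Abstract (Results) and Strengths and Limitations:** limit the trial's conclusions to feasibility and to relative effects in students of one university, and remove the claim about decreasing stigma in the public.
- **Generalizability sentence:** add that viewers are a convenience sample of 80 students aged 18-35 at a single university.

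No new data, visits or participants are needed, because the baseline scores are already planned. The cost is that the stated claims become less favourable. Keeping a claim about absolute effect would require an unexposed or neutral-video arm, which the present research question does not need.
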